## Abstract

**Background:**

The annual new-case detection rate for leprosy, while generally stable over the last decade, shows that transmission rates have remained stagnant despite the successful worldwide administration of multidrug therapy since the 1980s. As such, novel control strategies are urgently needed. Focusing on managing leprosy patient contacts, the most susceptible to contracting the disease, has been seen as a potential strategy in limiting the spread of leprosy as shown by a number of recent epidemiological studies. Immunoprophylaxis with Bacillus Calmette-Guérin (BCG) has been seen as an effective preventive measure due to its ability to stimulate the development of cellular immunity which is essential in controlling the disease, especially in its multibacillary (MB) forms. The association of immunoprophylaxis with chemoprophylaxis in a single dose of rifampicin has been shown to be a promising preventive strategy, although a variety of studies have found instances of early case detection just a few months after BCG vaccination.

**Methods/design:**

The present study is a phase IV chemoprophylactic clinical trial consisting of administration of a single dose of rifampicin in MB leprosy patient contacts under care at the Souza Araújo Outpatient Clinic/FIOCRUZ as part of a randomized (2:1), double-blind, placebo-controlled study. It is comprised of two groups: 1) rifampicin + BCG; and 2) placebo + BCG.

**Discussion:**

The aim is to evaluate whether the use of chemoprophylaxis with a single dose of rifampicin in MB leprosy patient contacts prior to the BCG vaccine would be able to prevent the onset of leprosy in those cases that may occur just a few months after vaccination. Contact subclinical infections (polymerase chain reaction) and the immunological parameters (anti-PGL-1, anti-LID-1, and IFN-γ) will be evaluated and the results will be compared after 12 months of follow-up.

**Trial registration:**

The Brazilian Registry of Clinical Trials (ReBEC), RBR-69QK5P. Retrospectively registered on 1 June 2017.

**Electronic supplementary material:**

The online version of this article (10.1186/s13063-018-2623-6) contains supplementary material, which is available to authorized users.

## Background

Following the introduction of multidrug therapy (MDT) in the 1980s, the global prevalence of leprosy drastically declined from more than 5 million cases worldwide to a little more than 200,000 in 2014. Likewise, over the last 10 years or so, the number of new global cases has markedly decreased from 299,036 in 2005 to 210,758 in 2015 [1, 2]. According to Lockwood and coworkers [3], the near-term goal regarding the elimination of leprosy needs to be revised primarily since India and Brazil continue showing high detection rates notwithstanding major advances in detection strategies, more easily accessible treatment, and constant innovation. The goal must above all be realistically achievable and based on proven scientific evidence and constant updating as new information emerges.

Brazil ranks second worldwide in the total number of leprosy cases, with India being the first. Brazil, however, takes first place in the Americas, where it was responsible for a full 92% of all new patients in 2015 [2]. According to Brazilian Ministry of Health (MH) data, 28,761 new leprosy patients were detected (14.7/100,000 inhabitants) in 2015. However, state-wide detection rates varied widely from 1.08/100,000 inhabitants in the State of Rio Grande do Sul to as high as 93.0/100,000 inhabitants in Mato Grosso State [4].

The pillars that sustain disease control measures are the administration of MDT to all newly detected leprosy patients along with close surveillance of their contacts. The prime objectives are early detection and timely treatment. Since 1991, the MH has recommended that the Bacillus Calmette-Guérin (BCG) vaccine be administered to all intradomiciliary contacts within 5 years of their index (primary) case diagnosis.

A study conducted in Brazil by Duppre and coworkers [5] showed that, despite the protection conferred by the BCG vaccine, a significant number of cases have occurred within a short period of time afterwards, mostly among contacts of multibacillary (MB) patients. Another study by Duppre et al. [6], using anti-PGL-I serology to assess the risk of becoming ill, found an excess of new leprosy cases within the first few months after vaccination, mainly among those positive for anti-PGL-1, indicating the presence of prior subclinical infection.

In 1989, Bagshawe et al. [7] reported that previous immunity to mycobacterial antigens was primarily responsible for the clinical manifestations of paucibacillary (PB) leprosy and that the nonspecific immune stimulation induced by BCG vaccination might precipitate clinical manifestations of leprosy in individuals with subclinical infection.

Another proposed measure of control is chemoprophylaxis among leprosy contacts via a single dose of rifampicin. The COLEP, a randomized, double-blind, placebo-controlled trial conducted in Bangladesh, observed a 57% risk reduction during the first 2 years of follow-up in conjunction with a higher protective chemoprophylactic effect among contacts of nonconsanguineous social contacts of MB index cases. Moreover, childhood BCG had a complementary effect on rifampicin, thereby reducing the number of contacts that became ill after vaccination [8]. These findings clearly indicate the need to evaluate the combined effect of BCG immunoprophylaxis and rifampicin chemoprophylaxis in contacts of new index cases.

In this same vein, a study by Richardus et al. [9] evaluated the protective role of BCG at the initial contact examination and 8 weeks later, in association with a single dose of rifampicin. Among the 5196 contacts included in the above study, 21 became ill (0.40%) 12 weeks after BCG, 12 of whom (57%) had no previous BCG scar, while 18 (87%) developed tuberculoid leprosy. These results are in line with those published by Duppre and coworkers [6].

In the area of serodiagnostics, the detection of IgM antibodies against phenolic glycolipid (PGL-1) represents the most reliable and highly evaluated standardized leprosy test available to date [10]. Nevertheless, leprosy IDRI (Infection Disease Research Institute) diagnostic-1 (LID-1), a novel protein (*Mycobacterium leprae,* ML0405, and ML2331), is considered to have diagnostic potential [11]. In parallel, polymerase chain reaction (PCR) has demonstrated greater sensitivity than bacilloscopy [12, 13]. It may be that the PGL-1, LID-1, and PCR combination is able to identify the most susceptible leprosy contacts.

Nonetheless, the immunoregulatory mechanisms involved in the early stages of the disease that could be targeted for the development of new tests have not yet been established. Moreover, the understanding of the impact of chemoprophylaxis on contacts is also limited due to the insufficiently described immunological profile of those who have been administered chemoprophylaxis, whether associated or not with immunoprophylaxis.

Besides, it is worth noting that the lack of a cell-mediated immune response to *M. leprae* antigens in individuals exposed to the infectious agent may be predictive of susceptibility. The production of interferon (IFN)-γ in peripheral blood mononuclear cells has been used as a measure of cellular responsiveness. A previous study by our group showed that the five contacts who developed leprosy during follow-up belonged to the group that was negative to or had reduced levels of IFN in response to mycobacterial antigens [14].

We report an ongoing study set out to assess the effectiveness of leprosy chemoprophylaxis with rifampicin among contacts of MB patients. The study will also assess the effect of rifampicin on laboratory parameters, namely anti-PGL-I, anti-LID-I, IFN-γ, and PCR, thought to indicate susceptibility to leprosy.

## Methods

### Study design

This is a phase IV, randomized (2:1), double-blind clinical trial involving either a single dose of rifampicin or placebo for the chemoprophylaxis of leprosy. Immunoprophylaxis with BCG as recommended by the Brazilian Leprosy Control Program was conducted in both comparison groups.

### Study site

The clinical trial will be carried out at the Ambulatory Souza Araújo (ASA) Outpatient Clinic associated with the Leprosy Laboratory of the Oswaldo Cruz Foundation. In partnership with the Leprosy Laboratory, the ASA is known for its clinical, laboratory, educational, and research activities in the areas of immunology, pathology, molecular biology, microbiology, and clinical practice, in addition to providing ready access to basic care and complex diagnostic tests. As a leprosy reference center, the ASA can optimize the performance of chemoprophylaxis and guide its future use in other health care units.

### Study population

Study participants are recruited from index case contacts already registered at the ASA who either live in the city of Rio de Janeiro or its metropolitan area. The clientele is mostly comprised of referrals from local health care services (both public and private) and those who arrive spontaneously.

After a leprosy diagnosis (clinical and/or bacteriological and/or histopathological), patients are informed about their clinical form, treatment regimen, mode of transmission, preventive measures, and the importance of presenting their contacts for clinical evaluation. All referrals made by the patient, whether consanguineous or not, household contacts, or those having close familial and/or social ties, are scheduled for a dermatoneurological examination as soon as possible after their index case diagnosis.

### Inclusion and exclusion criteria

The eligibility criteria are sufficiently broad to encompass most potential beneficiaries and yet protect the study from any selective or informational bias. The inclusion criteria are: 1) contacts of MB leprosy patients who agree to undergo chemoprophylaxis; 2) ages 6 months to 70 years; 3) an expressed willingness to undergo both clinical and anti-PGL-1 evaluations; 4) availability for follow-up; and 5) a firm commitment to return for vaccination within 2 months and be clinically evaluated at the end of 12 months. The minimum period for detecting the postulated effect will be 12 months.

Exclusion criteria are: 1) clinical or laboratory confirmation of leprosy at baseline; 2) BCG vaccination within the preceding 12 months (to prevent vaccine-related changes in the immune response), except for infants between 6 and 12 months of age (leprosy detection in infants indicates active transmission and the possibility of having other MB cases in the contact cluster); 3) contacts with immunosuppression and/or a history of tuberculosis in any of its forms; 4) pregnancy at any stage or refusal to undergo a urine pregnancy test; and 5) refusal to sign the informed consent form (ICF).

### Randomization and blinding

The allocation of the participants into groups is based on random sequence generation via computer software (WINPEPI program, version 11.18). The ratio is 2:1 with two intervention groups and one control group for the purpose of expanding the pool of information generated by chemoprophylaxis. Participants will be randomly assigned to intervention or placebo in permuted blocks of variable sizes defined by the statistician, concealed from team members. Blocked randomization guards against any imbalance in the number of participants assigned to each group, a major concern for interim analysis, and also protects against the temporal variations in individual characteristics as well as in study procedures that may arise in long enrollment phases.

The intervention code (rifampicin/placebo) for each patient is placed in sealed opaque envelopes and numbered sequentially (natural numbers). The envelopes are only opened after each contact has voluntarily signed the ICF to avoid foreknowledge of the allocated group. The number printed outside the envelope identifies the participant and the opened envelopes are saved to ensure traceability. Self-adhesive tags identifying the code of each volunteer are pasted onto the recruitment form, ICF, blood collection tubes, and each patient identification card. Group assignment will be concealed from study participants and from the researchers, physicians, and research assistants performing the study procedures (double-blind) as a way of protecting it from any unconscious biases or expectations as to the outcome. Two nonblinded team members that do not participate in data collection and analyses are responsible for dispensing rifampicin and the placebo, opening and storing envelopes for randomization, labeling study documents, and administrating the medications. The allocation ratio (2:1) will make the intervention group twice the size of the control group, thus hampering the blinding of the statistical analysis of the data.

Besides preventing informational bias, blinding may additionally avert adherence problems in the placebo group. During follow-up, unblinding will be allowed whenever the clinical management of adverse events requires disclosure of the individual’s group to the attending physician and to the independent monitoring committee.

### Intervention

All contacts included in the study receive a single supervised dose of rifampicin or placebo. Either rifampicin or placebo is administered during the initial visit, but only after each contact has signed the ICF, undergone anamnesis, been clinically examined, and had their data collected.

The rifampicin dose consists of 600 mg, or 10 mg/kg body weight in contacts weighing less than 40 kg. Infants and children receive the dosage in a solution determined by weight [15]. All contacts must receive the BCG vaccine a maximum of 2 months after the single dose of rifampicin or placebo.

Maintaining the blinding poses some challenges because rifampicin often leads to reddish-colored urine, tears, and sweat. Rifampicin and placebo capsules have identical organoleptic properties even though starch placebos do not mimic the reddish coloration in the urine and elsewhere.

### Outcomes

The primary outcome of the present study is the development of new leprosy cases during follow-up.

The assessment of clinical disease is based on the identification of cutaneous lesions, with observed changes in sensitivity and thickened nerves [16]. Clinical diagnoses are ascertained by professionals with leprosy expertise and include a dermatologist and a nurse responsible for the dermatological, clinical, and previous history evaluations, as well as a physiotherapist in charge of neurological assessment.

When the contacts return for evaluation, those with suspected clinical leprosy will be submitted to bacteriological and histopathological testing and then classified according to the Ridley and Jopling scale (1966) [17] as: borderline-borderline; borderline-lepromatous; lepromatous-lepromatous; tuberculoid; borderline-tuberculoid tuberculoid; or undetermined. Confirmed cases will also be grouped according to their grade of disability and bacilloscopic index (BI) as MB if BI-positive, or PB if BI-negative.

Secondary outcomes are: 1) the serological status of anti-PGL-1 prior and subsequent to chemoprophylaxis and before immunoprophylaxis; 2) the serological status of anti-LID-1 prior and subsequent to chemoprophylaxis and before immunoprophylaxis; 3) the PCR positivity, which is considered a marker of increased risk for developing leprosy; 4) IFN-γ production in response to *M. leprae* before and after chemoprophylaxis; 5) adverse events potentially associated with rifampicin; 6) intercurrent clinical conditions due to intervention; and 7) concordance between rapid test and serology for anti-PGL-1.

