### Adverse events

Adverse events and clinical complications will be monitored throughout the study period. The symptoms and signs temporally related to the intervention are recorded on a specific form, regardless of any presumed causal association with the intervention.

While the probability of the occurrence of adverse events related to the administration of a single dose of rifampicin is low, the most common ones have been loss of appetite, nausea, vomiting, diarrhea, and orange or reddish coloration of urine, saliva, feces, sweat, and tears. There may also be occurrences of colitis, facial flushing, hives, rashes, jaundice, liver failure, red spots on the skin, bleeding from the nose, gums, or vagina, anemia, flu symptoms, fever, weakness, headache, tremors, mental confusion, motor coordination disorders, transient visual changes, peripheral neuritis, and venous thrombosis [15].

Following blood collection, pain and bruising may take place at the puncture site, and auricular lobe lymph collection may also cause transient pain at the collection site.

In accordance with MH guidelines, BCG vaccination may lead to adverse reactions at the application site and in satellite lymph nodes, while severe systemic reactions [18] have very rarely been known to occur.

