### Statistical analysis

The evaluation of the efficacy of chemoprophylaxis will be based on the occurrence of new cases of leprosy in both groups and will be measured at least at 1 year after the single dose of rifampicin. Over the period of 1 year, three evaluations will be carried out: at baseline, 2 months, and 12 months.

The total number of randomized participants will be analyzed to preserve the safeguards against selection bias and confounding (“intention-to-treat analysis”). An alternative analytical strategy (“per-protocol analysis”) will disregard the data obtained from participants that did not meet the eligibility criteria and did not adhere to either of the intervention regimens or study procedures.

Evaluating the group that adhered to the protocol prevents classification bias that may result from analyzing the participants in the originally allocated group despite their not having followed the specifically planned procedures**.** Any discrepancies in the results of the two analytical strategies will be interpreted in light of the distribution of the baseline characteristics of the participants adhering to the protocol. The balanced distribution of covariates across comparison groups achieved by randomization could be lost as a result of violations in protocol.

The main explanatory variable defined by the study design is the intervention (rifampicin/placebo). Whereas univariate analyses will be performed to describe their baseline characteristics, bivariate analyses will explore the association between intervention and outcomes (response variables). Multivariate analyses (Cox regression) will be conducted to adjust the association estimates (hazard ratio for new cases) for covariates with any imbalance in group distribution. Subgroup analyses of effectiveness (derivatives of the measures of association) according to age, along with the BI and type of cohabitation with the index case, will be carried out.

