Cox regression is used to estimate the conditional hazard ratio and the survival function based on longitudinal data from a dynamic cohort of individuals under surveillance for different periods. The hazard ratio estimates the magnitude of the association between chemoprophylaxis and leprosy. The measurement takes into account the different time periods that have elapsed between exposure (treatment/placebo) and the outcome (illness) for each participant until disease develops or follow-up is discontinued [20]. The survival curve will be required to handle open and continuous recruitment as well as censorship, and the survival rates can be estimated by conditional probability according to the strategy proposed by Kaplan and Meier. The statistical significance will be assessed by the Log-Rank test [21].

For all the analyses, a 5% significance level will be adopted, and 95% confidence intervals constructed for the estimates.

An interim analysis will be conducted at the end of the third year of the study to evaluate individuals who have had at least 1 year of follow-up. This analysis will verify whether the cessation of participant recruitment is warranted by the data collected thus far and will be an opportunity to revise sample calculations according to the results. Interim analysis will seek evidence of the effectiveness, or lack thereof, of chemoprophylaxis or any clear indications that the postulated effect is so unlikely that recruitment is no longer justified. The assessment will be based on the number of events accumulated thus far and the trend in the difference between comparison groups, and the discontinuation of the trial will be submitted to the Data Monitoring Committee.

The critical level of a *z* score to reject the null hypothesis in the interim analysis will be adjusted to 2.782 (*p* = 0.005) in line with the O’Brien-Fleming protocol [22]. The conservative criterion in the interim analysis protects the study from the often-misleading results obtained from smaller samples.

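### The two safety outcomes are limited by presumed cause, although signs and symptoms are recorded regardless of cause; the arms should be compared on all recorded adverse events

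*Protocol article*

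**What the plan says.** The protocol article lists seven secondary outcomes under Outcomes. Two concern safety: "5) adverse events potentially associated with rifampicin; 6) intercurrent clinical conditions due to intervention". Both are worded by cause.

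Under Adverse events, collection is broader. "Adverse events and clinical complications will be monitored throughout the study period", and signs and symptoms with a temporal relation to the intervention are "recorded on a specific form, regardless of any presumed causal association with the intervention". The same section names vaccine reactions as adverse events: "BCG vaccination may lead to adverse reactions at the application site and in satellite lymph nodes", with severe systemic reactions described as very rare.

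Under Statistical analysis, bivariate analyses relate the intervention to the outcomes, so the listed outcomes are what the arms are compared on. Under Intervention, the article accepts that rifampicin often colours urine, tears and sweat, and that the starch placebo does not reproduce this.

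**The concern.** In a randomised, placebo-controlled comparison the control arm already answers the causal question: an excess over placebo is the evidence of an effect. Selecting events by presumed cause before comparing the arms puts an opinion, or a list of expected effects, ahead of that evidence.

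Two things can then go wrong. If whoever applies the filter has a clue to the arm, the same nausea or headache may be counted more readily on rifampicin than on placebo, and a difference appears where none exists. Conversely, a real effect that nobody expects of rifampicin may never enter the outcome. At stake is the interpretation of the safety comparison. The primary leprosy outcome is not touched.

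**Working it through.** The plan states no figure on this point, so there is none to reproduce. The check is a comparison of sections, followed by an illustration on assumed rates.

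**Sections side by side**

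1. Collection (Adverse events): temporally related signs and symptoms, "regardless of any presumed causal association with the intervention".
2. Outcome definition (Outcomes): events potentially associated with rifampicin, and conditions due to intervention.
3. Comparison (Statistical analysis): by arm, on the outcomes.

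Items 1 and 2 differ by a causal filter, and item 3 applies the comparison after the filter.

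4. Blinding (Intervention): discoloration is a possible clue to the arm. The Adverse events section also lists it among the most common effects of rifampicin, so the clue may come to light in the same interview that elicits the other events.
5. Scope of the word intervention: the Statistical analysis section uses it narrowly ("The main explanatory variable defined by the study design is the intervention (rifampicin/placebo"), as does the intervention code under Randomization and blinding. Study design treats BCG as common to both arms: "Immunoprophylaxis with BCG as recommended by the Brazilian Leprosy Control Program was conducted in both comparison groups". Yet the section headed Intervention also covers the BCG dose, the Abstract describes the groups as rifampicin + BCG and placebo + BCG, and the Discussion speaks of separate interventions. Whether outcome 6 covers BCG reactions is therefore unclear.

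**How a differential filter acts**

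Let p be the true event rate, equal in both arms, and let a_R and a_P be the shares of events attributed on rifampicin and placebo. The outcome then shows p × a_R against p × a_P. The apparent risk ratio is a_R / a_P whatever p is, and it equals 1 only if attribution is the same in both arms.

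Arm sizes are from Calculation of sample size: 995 and 498 (total 1493). All participants are assumed to contribute. The values of p, a_R and a_P are **assumptions; none is in the documents**.

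*Single results*, pooled two-proportion test, with SE = √[p̄(1 − p̄)(1/995 + 1/498)]:

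- p = 10%, a_R = 60%, a_P = 30%: 6.0% v 3.0%, about 60 v 15 contacts. p̄ = (59.7 + 14.94)/1493 = 0.0500; SE = 0.01196; z = 0.030/0.01196 = 2.51; p-value 0.012.
- p = 10%, a_R = 48%, a_P = 30%: 4.8% v 3.0%. p̄ = (47.76 + 14.94)/1493 = 0.0420; SE = 0.01101; z = 0.018/0.01101 = 1.63; p-value 0.10.

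*Chance of a spurious significant excess on rifampicin*, two-sided 5%, a_P = 50%, from Φ[(difference − 1.96 × SE under no difference) / SE under the difference]:

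| True rate p | a_R = 70% | a_R = 80% | a_R = 90% |
|---|---|---|---|
| 5% | 17% | 31% | 47% |
| 10% | 31% | 58% | 80% |
| 20% | 60% | 90% | 99% |

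Example for p = 10%, a_R = 70%: 7.0% v 5.0%; SE under no difference 0.01337; SE under the difference 0.01268; (0.020 − 1.96 × 0.01337)/0.01268 = −0.49; Φ = 0.31.

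Without a filter, an equal true rate gives an equal expected count in each arm and about the nominal error. This holds only if recording itself does not depend on the arm and discoloration is left out of the count.

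**The case against.** The best defence is that the article describes no attribution step: no assessor, no causality scale, no rule. Outcome 5 could simply mean events of the kinds listed under Adverse events, in which case there is little judgement to bias, and coding rules may sit in a fuller document. This stands in part. A case-by-case judgement is a natural reading but not a stated procedure. A fixed list, however, would still exclude unlisted events, and a later document that follows this outcome definition inherits its causal wording.

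It is also fair that physicians and assistants are blinded, that nothing in the documents supports any particular attribution gap, and that the milder illustration gives only p = 0.10.

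A third objection is that counting all events does not cure unblinding. Discoloration could also influence what participants report and what staff write down, and because it is itself a listed adverse event it would create an arm difference on its own. Both points are right. The second is met by reporting discoloration separately. The first remains, but a causal filter adds a further step open to the same influence.

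Three stronger readings are tempting, and the documents do not support them:

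- *BCG reactions go uncounted.* They are named as adverse events, and adverse events are monitored throughout. The term intervention can be read to include BCG. What is shown is ambiguity in the outcome, not exclusion.
- *The 2-month interval shows that rifampicin may alter BCG reactions.* The stated reason concerns the immune response to the live vaccine, not its adverse reactions.
- *The monitoring committee decides without adverse events by arm.* The interim text, "The assessment will be based on the number of events accumulated thus far and the trend in the difference between comparison groups", describes an effectiveness and futility assessment. It does not list everything the committee receives, and the article allows an individual's group to be disclosed to the independent monitoring committee when managing an adverse event.

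**Conclusion.** The point holds as a flaw in the definition of secondary outcomes 5 and 6. The causal restriction is in the text, collection is wider than the outcome, and the article itself concedes a threat to the blind. The restriction may therefore act differently by arm, and it may miss unsuspected effects.

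The size of any bias cannot be derived from the documents. The 17% to 99% range in the illustration depends wholly on the assumed event and attribution rates, and the bias is zero if attribution is equal in both arms. The conclusion also assumes that the causal wording will be applied as a filter, which is what it says, even though no procedure is given. This is a correction worth making to a secondary outcome. It does not bear on the primary result, the sample size or the conduct of the interim analysis.

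**What to change.** Redefine secondary outcomes 5 and 6 as all recorded adverse events, compared by randomised arm regardless of causality. Then:

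- report discoloration separately, outside the overall count;
- keep causally attributed events as a descriptive subset only;
- state explicitly that recorded events after BCG are included, BCG reactions among them, so that the result does not turn on what intervention means.

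The change is one of outcome wording and tabulation. It alters no visit or sample size. Its downside is that background illness enters the counts in both arms and may dilute a real difference. One check is needed first: the form covers signs and symptoms temporally related to the intervention and the article gives no time window, so it must be confirmed that the form captures events after BCG. If it does not, the change also requires an extension of the form.
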